### Date management

Cognitive function and the severity of psychotic symptoms will be assessed by two clinical psychiatrists who remain blinded to the group allocation. All demographic data and scale-related information will be recorded in electronic CRFs and stored on a designated website. Access to these securely stored CRFs will be restricted to the project leader and the principal investigator. To ensure patient confidentiality, pseudonymization will be employed by substituting real patient names with unique identification numbers during data entry. Although the trial does not incorporate a data monitoring committee, oversight of the subject group is entrusted to a designated individual. Patient adherence to tDCS or MT sessions will be facilitated through notifications sent via WeChat.

### Statistical methods

The Shapiro-Wilk Test will be used to analyze whether the data conform to normality. If the quantitative data conform to a normal distribution, they will be expressed as the mean and standard deviation (SD); if they do not, they will be displayed as median values and interquartile range (IQR). Categorical data will be presented as counts with percentages. To evaluate differences in baseline characteristics between groups, t-tests, nonparametric tests, chi-square tests, Mann-Whitney U tests, and ANOVA will be employed appropriately. The Fisher exact test or χ² test will be used to compare adverse effects between groups.

In accordance with the CONSORT guidelines, analyses will be conducted following the intention-to-treat (ITT) principle, whereby all participants will be analyzed as originally randomized. A line graph will be utilized to depict values across different time points. To evaluate between-group and within-group differences over time for both primary and secondary outcomes, we will appropriately apply generalized linear mixed models and repeated measures ANOVA. A stepwise model selection process will be utilized to identify a parsimonious multivariable regression model. Age, gender and DDD doses of antipsychotic medications will be included as covariates in all models. The likelihood ratio test (LRT) will be utilized to assess the treatment effect by determining whether the coefficients for both the treatment and the interaction between time and treatment in the model are equal to zero. To account for multiple comparisons across multiple time points, p-values will be adjusted using the Bonferroni correction method. All statistical analyses will be conducted using SPSS 20.0. P < 0.05 is considered to be a statistically significant difference.

To minimize the impact of antipsychotic medications on clinical outcomes, several measures will be taken. First, all participants had been on a stable dose of antipsychotic medication for at least two weeks prior to the trial, and the doses of these medications remained unchanged throughout the study. This approach is consistent with previous studies (41), as maintaining a stable dose of antipsychotic medication helps reduce variability in drug effects during the intervention period. Second, we will adopt the Defined Daily Dose (DDD) method to standardize the doses of different antipsychotic medications across groups. By converting the actual doses of various antipsychotics into DDD units, we will compare and ensure that the drug doses are equivalent across different groups after randomization. Third, we plan to include the DDD doses as a covariate in the models to ensure the accuracy of the study and the reliability of the results.

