## Method

### Study design

This is a prospective, single-center, randomized, double-blind, sham-controlled study designed to assess the effects of tDCS combined with MT on the improvement of cognitive functions in patients with schizophrenia. Eligible participants will be recruited and randomly allocated into five groups in equal proportions (1:1:1:1:1): active tDCS combined with MT group (Group 1), sham tDCS combined with MT group (Group 2), active tDCS group (Group 3), MT group (Group 4), and control group (Group 5). Assessments will be conducted at baseline (T0), after 2 weeks (T1), and after 4 weeks (T2). The study design is depicted in **Figure 1**.

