### Sample size calculation

The sample size was calculated using G*Power software (G*Power, Version 3.1.9.7) based on a previous study (38). The study parameters include a Type I error rate of 0.05, a statistical power of 80%, and an effect size of 0.25. Based on these calculations, the required sample size was determined to be 45 participants using a repeated measures analysis of variance (ANOVA) model. Accounting for an estimated 20% dropout rate, a target sample size of 60 patients (12 per group) was established. Consistent with the previous literature by Emuk et al. (39), they also planned to include 12 participants per group, for a total of 60 participants. Here are the main reasons: When designing a pilot investigation where there is no prior information upon which to base the sample size, the recommendation would be a sample size of 12 per group as being appropriate. Three reasons for justifying a sample size of 12 per group will be given based on feasibility, gains in the precision about the mean and variance, and regulatory considerations (40). This sample size is expected to provide adequate statistical power to address the study objectives.

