### Harms

To assess the safety and potential adverse effects of tDCS, this study will systematically analyze both serious and non-serious adverse events. Following each tDCS session, all participants will be required to complete the tDCS Adverse Events Questionnaire. Commonly reported side effects include sensations of tingling, mild erythema, itching, and discomfort at the site of stimulation. Participants will evaluate their adverse experiences on a scale ranging from 0 to 5. All adverse events will be recorded in the case report form (CRF). The tDCS device will be administered by a therapist with specialized training and experience in its application. Consequently, it is anticipated that participants will not encounter any significant health risks or adverse events. In the event that a serious adverse event does occur, the participant will be withdrawn from the trial, and the incident will be reported to the ethics committee.

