The main innovation of this study is that the combination of tDCS targeting mPFC and MT may have synergistic effects to enhance cognitive improvement in patients with schizophrenia. tDCS targeting mPFC modulates t cortical excitability, thereby enhancing prefrontal activity and promoting neuroplasticity. MT can activate mPFC, which plays a crucial role in memory and attention processes, thereby potentially amplifying the effects of tDCS (57). The integration of tDCS and MT may present a novel therapeutic strategy designed to enhance cognitive rehabilitation efforts. Furthermore, this approach minimizes physical discomfort and potential side effects for patients and can be easily administered in a home setting, thereby increasing the convenience and accessibility of treatment. Additionally, the relatively low cost of tDCS and MT makes this treatment method more economically feasible compared to more complex neuromodulation techniques, such as transcranial magnetic stimulation. The integration of tDCS and MT is based on the observation that they share the similar mechanisms of action at the neural level, specifically through the modulation mPFC activity and neuroplasticity. The application of tDCS during music listening appears to enhance neural responses that are otherwise suppressed when tDCS is administered alone. Hence, if we can demonstrate combining tDCS with MT enhances cognitive improvement in schizophrenia, it might alleviate the disease burden and improve patient health outcomes.

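### The only named comparison of adverse effects is a Fisher or chi-square test, which at 12 per arm says little about tolerability and does not suit 0-5 ratings taken after every tDCS session

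*Protocol article*

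**What the plan says.** The Statistical methods section gives one sentence to the comparison of safety between arms: "The Fisher exact test or χ² test will be used to compare adverse effects between groups". It does not say whether the test is pairwise or across all five groups, or which comparison matters most. The general threshold at the end of the section is "P < 0.05 is considered to be a statistically significant difference". The multiplicity rule concerns time points ("To account for multiple comparisons across multiple time points, p-values will be adjusted using the Bonferroni correction method") and does not mention adverse effects.

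The Harms section sets a wider aim: "To assess the safety and potential adverse effects of tDCS, this study will systematically analyze both serious and non-serious adverse events". A questionnaire follows each tDCS session, and "Participants will evaluate their adverse experiences on a scale ranging from 0 to 5". The tDCS section gives one session a day, five days a week, for four weeks, which is 5 x 4 = 20 sessions. Table 3 also schedules an Adverse Reaction Scale at weeks 2 and 4.

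On numbers, "a target sample size of 60 patients (12 per group) was established". Groups 1 and 3 receive active tDCS and Group 2 receives sham; Groups 4 and 5 have no tDCS sessions.

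**The concern.** The named tests work on categories, while the main tolerability data are graded and repeated. The Harms section lists tingling, mild redness, itching and discomfort as commonly reported. For effects of that kind, how strong they are and how often they recur tell more than whether they ever occurred. If the test is applied in its usual way, to patients with and without an event, both features are lost.

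The arms are also small. A test with little chance of reaching significance will usually return a non-significant result whether or not active tDCS is worse than sham. The Discussion already describes the combination favourably ("this approach minimizes physical discomfort and potential side effects for patients and can be easily administered in a home setting"). A reader who meets a non-significant safety comparison beside that statement could take it as support that the data cannot give.

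**Working it through.** **The plan's own figure.** The sample size rests on efficacy: alpha 0.05, power 80%, effect size f = 0.25, repeated measures ANOVA. For the group-by-time interaction with 5 groups and 3 measurements, assuming a correlation of 0.5 and no sphericity correction (neither is stated), power at N = 45 is 0.810. No smaller multiple of 5 reaches 80%. Allowing for dropout, 45 / (1 - 0.20) = 56.25, so 57; the next multiple of 5 is 60. The stated figure reproduces. No power is stated for safety.

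**What 12 against 12 can detect.** Take k events on active tDCS and none on sham. The two-sided Fisher p-value is 2 x C(12,k) / C(24,k).
- k = 4: 2 x 495 / 10,626 = 0.093.
- k = 5: 2 x 792 / 42,504 = 0.037.

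So 33% against 0% is not significant by Fisher, and 5 of 12 against 0 is needed. The uncorrected chi-square for the k = 4 table is 24 x (4 x 12)² / (12 x 12 x 4 x 20) = 4.8, p = 0.028. The two tests allowed by the sentence can thus disagree on the same data.

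**Power for an assumed 30-point excess.** These figures come from exact enumeration of all tables, two-sided at 0.05.

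| Comparator vs active, 12 v 12 | Fisher | Uncorrected chi-square |
|---|---|---|
| 0% v 30% | 0.28 | 0.51 |
| 10% v 40% | 0.23 | 0.39 |
| 20% v 50% | 0.21 | 0.36 |
| 30% v 60% | 0.21 | 0.36 |

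- Over comparator rates from 0% to 70%, Fisher runs from 0.21 to 0.28 and uncorrected chi-square from 0.36 to 0.51. The Yates-corrected test matches Fisher here.
- With about 10 v 10 after 20% dropout, Fisher falls to 0.12-0.16.
- A five-group chi-square (simulated, comparator rates 10% to 30%) has about 0.42-0.57 if both active arms carry the excess, and 0.30-0.47 if only one does.
- Pooled active against sham (24 v 12), Fisher has 0.30-0.44 for comparator rates of 0% to 50%.
- For 80% power in a pairwise comparison at comparator rates of 10% to 35%, 32 to 43 patients per arm would be needed without continuity correction.

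**What a clean arm shows.** With no events in n patients, the upper end of the exact two-sided 95% interval is 1 - 0.025^(1/n): 26% for n = 12 and 14% for n = 24.

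**What a yes/no count loses.** If an effect occurs in a session with probability p, and sessions are taken as independent, the chance that a patient ever reports it in 20 sessions is 1 - (1 - p)^20. This is 64% at p = 5%, 88% at 10% and 99% at 20%. A doubling from 10% to 20% per session shrinks to 88% against 99% per patient. Correlation within patients would soften this, but the tendency to fill up in both arms remains.

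**Illustration with the score.** Suppose a normal score with equal SDs, and for the count a split midway between the two arm means. A 1-SD shift then gives 69% v 31%; Fisher has 35% power (12 v 12) or 49% (24 v 12), against 65% or 78% for a t test on the score. For a 0.5-SD shift (60% v 40%) at 12 v 12 the figures are 9% and 22%. The protocol proposes no such split, and real ratings may be skewed with many zeros, so this shows direction only.

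**The case against.** Fisher's exact test is a conventional and valid choice for sparse adverse-event counts. Safety is not among the three objectives in the Background, the sample size was set for efficacy, and the limitations paragraph admits that small groups may reduce power. Low power for safety is therefore inherent in a trial of this size and would not by itself be a finding. All of this stands. It also stands that the score analysis does not cure low power: it has only 22% for a 0.5-SD shift at 12 v 12.

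Three stronger readings are tempting, and the documents do not support them.
- A reader might infer that non-significance will be read as safe. Nothing in the article says so; the threshold of 0.05 is a general one, and the favourable sentence in the Discussion is rationale, not a conclusion tied to this test.
- A reader might infer that the 0-5 scores will go unused or be cut to yes/no. The article names no between-group analysis of them, but it promises systematic analysis of adverse events and gives general rules for summarising quantitative data. Further detail may sit in a full protocol or analysis plan that is not shown.
- A reader might infer that the named tests miss a 30-point excess about 8 times in 10. That is roughly right only for pairwise Fisher or Yates (72-79% missed). Uncorrected chi-square misses 49-64%, and a five-group chi-square about 43-70%.

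What survives is the mismatch between the one comparison that is named and the graded, repeated data that are collected.

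**Conclusion.** The point holds as a minor one. A non-significant result would be uninformative about tolerability: every version of the named test is weak at this size for an assumed 30-point excess, and an event count uses neither the intensity nor the recurrence of the effects recorded. The event rates and the size of the excess are assumptions, and two-sided testing is assumed because the article does not state it. The conclusion does not rest on any one rate, since Fisher power stays between 21% and 28% across the comparator rates examined.

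**What to change.** Before data lock, amend the adverse-effect sentence in Statistical methods as follows.

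1. Keep the counts, and report for each event the proportion of patients affected with an exact 95% interval, per arm and pooled over active tDCS. The Fisher test can stay beside these.
2. Make the main tolerability comparison each patient's mean and maximum 0-5 score over sessions, active tDCS (Groups 1 and 3) against sham (Group 2), as a difference with a 95% confidence interval. Use a rank-based or bootstrap interval if scores are skewed or mostly zero.
3. State that p > 0.05 on any adverse-effect comparison is not evidence of safety.

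The cost is slightly more analysis, with no extra patients, visits or data. Pooling Groups 1 and 3 assumes that music does not alter the local effects of tDCS, and sham is given only with music, so show the per-arm figures as well.

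### The primary model is left open: unspecified stepwise selection, and two model families with neither named as primary, so the 5% error rate and the ITT population are not assured

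*Protocol article*

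**What the plan says.** All the analysis statements are in the protocol article, Statistical methods.

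- Models for primary and secondary outcomes: "we will appropriately apply generalized linear mixed models and repeated measures ANOVA". No rule says which applies to the primary outcome, the change in MCCB.
- Selection, in the next sentence: "A stepwise model selection process will be utilized to identify a parsimonious multivariable regression model". Candidates, entry or removal criterion, and protected terms are not given.
- Covariates: "Age, gender and DDD doses of antipsychotic medications will be included as covariates in all models".
- Test: a likelihood ratio test of whether the treatment and time-by-treatment coefficients are all zero.
- Population: "analyses will be conducted following the intention-to-treat (ITT) principle, whereby all participants will be analyzed as originally randomized".

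The Sample size calculation section bases the trial on the second model family: "the required sample size was determined to be 45 participants using a repeated measures analysis of variance (ANOVA) model". It then states: "Accounting for an estimated 20% dropout rate, a target sample size of 60 patients (12 per group) was established".

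**The concern.** Two features leave the headline analysis unsettled.

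First, stepwise selection uses the outcome data to decide which terms stay. A p-value computed afterwards as if the model had been fixed in advance does not carry its nominal error rate. The text does not say whether selection acts only on additional covariates or also on arm terms. It also does not say whether the likelihood ratio test is applied to the full or the reduced model.

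Second, the two model families treat missing visits differently. A likelihood-based mixed model uses each patient's observed visits. Standard repeated measures ANOVA omits anyone with a missing visit. With dropout expected, the two can give different answers for the same primary outcome, and no rule says which one counts. ANOVA is not a remote option, because the sample size rests on it.

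At stake are the error rate of the primary test, and whether the result describes all randomised patients or only those who completed.

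**Working it through.** **1. The plan's own sample size.** Inputs from Sample size calculation: "The study parameters include a Type I error rate of 0.05, a statistical power of 80%, and an effect size of 0.25". From Study design: k = 5 groups and m = 3 measurements. Correlation between repeated measures (rho) and the sphericity correction are not stated; I assume rho = 0.5 and no correction.

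For the within-between interaction:
- lambda = f² × N × m / (1 − rho)
- df1 = (k − 1)(m − 1)
- df2 = (N − k)(m − 1)

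At N = 45, lambda = 0.0625 × 45 × 3 / 0.5 = 16.875, df1 = 8, df2 = 80, and power is 0.810. The stated 45 is reproduced. It depends on rho: 0.3 requires 61 (65 in equal groups) and 0.7 requires 29 (30 in equal groups).

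Dropout: 45 / (1 − 0.20) = 56.25, rounded up to 57, which becomes 60 in five equal groups. The target is consistent.

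**2. Patients left if ANOVA is used without imputation.** 60 × 0.80 = 48, or 12 × 0.80 = 9.6 per group, assuming every dropout misses at least one visit. Under the same formula:
- 48 patients: lambda = 18, df2 = 86, power 0.842
- 60 patients: lambda = 22.5, df2 = 110, power 0.930

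So listwise deletion does not take planned power below 80% at the rho that reproduces 45. What it changes is who is analysed.

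**3. Effect of selection on type I error.** The document does not describe the procedure, so this is an illustration under assumptions:
- 60 patients in five arms of 12, one change score, no treatment effect.
- Three forced covariates, standing in for age, gender and DDD dose.
- Forward entry at p < 0.05 over 3, 6 or 10 pure-noise candidates, all independent normal.
- F tests in place of the likelihood ratio test.
- 6,000 replicates per setting. Monte Carlo standard error is √(0.05 × 0.95 / 6000) = 0.3 points near 5%, and √(0.18 × 0.82 / 6000) = 0.5 points near 18%.

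| Noise candidates | No selection, joint treatment test | Treatment forced, others selected | Arm terms also candidates: at least one retained |
|---|---|---|---|
| 3 | 5.0% | 5.7% | 17.8% |
| 6 | 4.8% | 5.9% | 18.5% |
| 10 | 4.9% | 7.0% | 18.5% |

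With treatment forced, the excess over 5% is 0.7 to 2.0 points. A separate run of this case gave about 4.7% with 3 candidates and 6.4% with 10, so the inflation is modest and may be negligible with few candidates.

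The last column counts retention of any arm term, which is not the plan's joint test. Most of it is multiplicity across indicators: screening four non-reference arm indicators alone gave 17.6%, against 5.1% for their joint 4-df test.

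**The case against.** The strongest reply is that the section can be read coherently. The three covariates are forced, selection acts on other terms, and a joint test of treatment and time-by-treatment presupposes that both are in the model. Mixed models are named first and keep partial data, the ITT commitment is explicit, and no section plans a completers analysis. Missing-data handling may sit in an analysis plan that is not shown. Under Blinding, analysts see only coded groups until the analysis is finished, which limits steering towards a favoured arm.

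Much of this stands, and it rules out several stronger readings that a reader might infer:

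- *That the stepwise sentence contradicts the fixed covariates.* The two can be reconciled as above; they are unreconciled in the text, not incompatible.
- *That about one null trial in five would yield a treatment effect.* A figure of 21% arises if five separate arm indicators compete for entry at p < 0.05. No section describes that, and the stated test is a single joint one.
- *That the trial will report completers only.* This follows only if repeated measures ANOVA is used without imputation.
- *That dropout breaks the planned power.* The increase from 45 to 60 exists to absorb it.

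What the reply does not remove is that stepwise selection is a stated method, not a missing detail, and protection of the treatment terms is implied at most. Coded groups do not prevent a choice between models by p-value.

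**Conclusion.** The point holds in limited form. The protocol commits to outcome-driven selection for its efficacy models and names two unranked model families for one primary outcome. The 5% error rate is therefore not assured. The illustrative size is about 6-7% on the more natural reading, with treatment forced in. It is about 18% or more if arm terms are candidates, which the text does not explicitly exclude. These figures rest on an assumed forward procedure, a single change score and independent noise covariates. They show direction and range, not this trial's actual error rate.

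The conflict with ITT is conditional on ANOVA without imputation. It would then affect about 12 of 60 patients (60 − 48). The harm would be possible bias and a changed analysis population. Power would remain about 0.84 at the assumed rho of 0.5.

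**What to change.** In Statistical methods:

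1. Delete the stepwise sentence for all treatment comparisons.
2. Name one primary analysis of MCCB: a mixed model using all available data from all randomised participants, with treatment, time, their interaction, age, gender and DDD dose fixed and no selection. Apply the joint likelihood ratio test to that model.
3. Keep repeated measures ANOVA only as a sensitivity analysis, labelled as completers.

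This changes analysis wording only; sample size and visits are unaffected. The downside is a slightly less parsimonious model. The change should be made and documented before any unblinding, including the first release of coded groups.

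### The likelihood ratio test that decides the treatment effect has a false-positive rate of about 8–11% at 12 patients per arm, not the stated 5%

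*Protocol article*

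**What the plan says.** The Statistical methods section names one test for the treatment effect: "The likelihood ratio test (LRT) will be utilized to assess the treatment effect". Its null hypothesis is that the treatment and time-by-treatment coefficients are all zero. The threshold in the same section is: "P < 0.05 is considered to be a statistically significant difference". Generalized linear mixed models and repeated measures ANOVA are both named as models, and age, gender and the antipsychotic dose in DDD units enter every model. A Bonferroni adjustment is planned for comparisons across time points. No covariance structure, reference distribution or small-sample correction is given.

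The Study design section sets five equal arms and three assessments (T0, T1, T2). On size, the Sample size calculation section says "a target sample size of 60 patients (12 per group) was established", allowing for 20% dropout. The calculation used "a Type I error rate of 0.05, a statistical power of 80%, and an effect size of 0.25" in a repeated measures ANOVA.

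**The concern.** A likelihood ratio test of fixed effects compares two maximum-likelihood fits. Their variance estimates divide by the number of patients and make no allowance for the coefficients fitted, so the residual variance is underestimated, more so in the larger model. The chi-square reference ignores this and is accurate only when patients greatly outnumber coefficients. Here up to 12 coefficients are tested, on top of three covariates, with 12 patients per arm.

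At stake is the error rate of the test that the protocol makes decisive. If no arm differs from any other, the trial would still report a treatment effect more often than its threshold promises. The Bonferroni step acts on later time-point comparisons and does not recalibrate the joint test.

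**Working it through.** **Inputs.** Five arms, three visits, 60 patients (12 per arm), 20% dropout, three covariates, alpha 0.05: all from the protocol. Assumed: normal outcomes, visit correlation 0.5–0.8, maximum-likelihood fits and the usual chi-square reference.

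**The plan's own sample size.** For the group-by-time interaction in a repeated measures ANOVA, the noncentrality is f²·N·m/(1 − ρ). Taking the effect size as Cohen's f, with ρ = 0.5 and sphericity (neither is stated), N = 45 gives 0.0625 × 45 × 3 / 0.5 = 16.875. With 8 and 80 degrees of freedom the power is 0.810; at N = 40 it is 0.745. So 45 is reproduced, and 45/0.8 = 56.25, i.e. 57, rounded up to 60. That calculation rests on an F test with finite denominator degrees of freedom. The likelihood ratio test named for the analysis has no such protection.

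**Coefficients tested.** Treatment: 5 − 1 = 4. Treatment by time: 4 × 2 = 8. Total 12 if T0 is an outcome row. If T0 is a covariate and only T1 and T2 are modelled: 4 + 4 = 8.

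**Analytic check (unstructured covariance, covariate effects allowed to differ by visit).** The statistic behaves approximately like chi-square multiplied by N/w, where w = N − p − (m − q + 1)/2. Here p is the number of regression columns, m the number of visits modelled and q = 4.

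- 12 df, N = 60: p = 1 + 3 + 4 = 8 and m = 3, so w = 52 and 60/52 = 1.154. The critical value 21.03 acts like 21.03/1.154 = 18.22, and P(χ²₁₂ > 18.22) = 0.109.
- 8 df, N = 60: p = 9 (baseline added) and m = 2, so w = 51.5 and 60/51.5 = 1.165. Then 15.51/1.165 = 13.31, and P(χ²₈ > 13.31) = 0.102.
- 12 df, 60 × 0.8 = 48 completers: w = 40 and 48/40 = 1.20. Then 21.03/1.20 = 17.52, and P(χ²₁₂ > 17.52) = 0.131.

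**Simulation with no effect.** Each setting had 4,000 to 20,000 trials (Monte Carlo error about 0.2–0.5 points). Ranges span repeated runs and visit correlations. Nominal rate 5%.

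| Model | N = 60 | N = 50 | N = 45 |
|---|---|---|---|
| T0 as outcome, 12 df, unstructured, covariate effects by visit | 10.7–11.2% | 12.3–12.9% | 13.5–14.3% |
| T0 as outcome, 12 df, unstructured, common covariate effects | 9.2% | – | – |
| T0 as outcome, 12 df, random intercept | 7.7–8.2% | 8.8–9.2% | 9.2–9.5% |
| T0 as covariate, 8 df, unstructured, covariate effects by visit | 9.9–10.3% | 11.4–11.9% | 12.2–12.8% |
| T0 as covariate, 8 df, unstructured, common covariate effects | 8.9% | – | – |
| T0 as covariate, 8 df, random intercept | 8.4–9.1% | 9.1–9.5% | 9.8–10.1% |
| Common baseline mean, 8 df, unstructured | 8.7% | – | – |

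The N = 50 and N = 45 columns shrink the whole sample. When the earlier visits of dropouts are kept (60, 54 and 48 patients at T0, T1 and T2; unstructured), the rate is 12.4% with 12 df and 11.4% with 8 df.

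**Is the reference distribution the cause?** With the statistic scaled by w/N (Bartlett correction), the rate at N = 60 falls from 11.2% to 5.0% (12 df) and from 9.9% to 4.9% (8 df). An F test with finite denominator degrees of freedom gave 5.1–5.6%.

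**The case against.** **The article does not write chi-square.** Reference distributions and degrees of freedom are often left to an analysis plan, which is not shown. The chi-square reference is therefore an inference. But it is the standard one for a likelihood ratio test, and the article goes beyond silence: it fixes the test, the joint hypothesis and the threshold. Applied as written in the ordinary way, they do not give 5%.

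**The size depends on an unstated model.** This stands. The 11% end needs an unstructured covariance with covariate effects that differ by visit. A random intercept gives about 8–9%. Describing the inflation as a doubling suits only the unstructured fits.

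**Repeated measures ANOVA is also named, and its F tests use finite degrees of freedom.** True, but the treatment effect is assigned to the likelihood ratio test.

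**The omnibus rate is not the rate of falsely claiming the trial's hypothesis,** which is that the combination beats each single treatment. This also stands. Suppose a significant 8-df test had to be followed by Bonferroni-adjusted T2 contrasts of the combination against each single treatment. In an illustrative null simulation at least one favourable contrast then appeared in 1.3% of trials, and both in 0.1%. The article states no such gating, however, and makes the omnibus test the assessment of the treatment effect.

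**It is a proof-of-concept study with an acknowledged small sample.** That tempers the consequence but does not justify a threshold that is not met. The Discussion treats a confirmed hypothesis as offering an effective therapeutic strategy.

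**Conclusion.** The concern holds. At the planned 60 patients the named test has a type I error of about 8–11% (7.7–11.2% over all models tried), which is 1.5 to 2.2 times the stated 5%. This is a separate matter from the handling of T0, because 8.4–10.3% remains with baseline as a covariate. Dropout raises the rate clearly for unstructured fits and only slightly for a random intercept.

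The figures assume normal outcomes and an uncorrected chi-square reference. The stepwise model selection planned in the same section was not simulated, so its effect is not included. The excess applies to the omnibus test; the rate for specific claims about the combination depends on follow-up contrasts that the article does not fix.

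**What to change.** Replace the likelihood ratio sentence in Statistical methods with one of two options, chosen before unblinding:

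1. Test the same treatment and treatment-by-time coefficients jointly with an F test from a REML fit, using Satterthwaite or Kenward-Roger denominator degrees of freedom, and name the covariance structure.
2. Keep the likelihood ratio statistic but take its p-value from re-randomising the arm labels 12:12:12:12:12. This mirrors the allocation in the Randomization section, which sorts 60 patients at random into five groups of 12.

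The cost is one sentence and no new data. P-values become somewhat larger, because the present ones are too small.
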